**Primary outcomes**

1. Percent of ED encounters screened for HRSNs. The numerator will be an ED encounter with any indication of HRSN screening using any tool or questionnaire, regardless of patient completion or results. The denominator will be all eligible ED encounters (see **Inclusion criteria**, above). IU Health uses the PRAPARE screening tool^53^, which is recorded in the EHR. Eskenazi Health uses the screening tool included in the Epic EHR, which is also recorded and accessible to our study team.
2. Percent of ED encounters that were referred for HRSN services. The numerator will be ED encounters with a referral to social worker, case management, community health workers, or related services within 24 hours of the ED encounter (see Appendix B). The denominator will be all eligible ED encounters (see **Inclusion criteria**, above).

**Secondary outcomes**

3a. Percent of encounters with an ED revisit measured at 3 days. The numerator will be an ED encounter at any facility included in the INPC database within 3 days of an ED encounter at an intervention or comparator site. ED revisits may serve as the index visit for subsequent revisits. The denominator will be all eligible ED encounters (see **Inclusion criteria**, above). Encounters resulting in an inpatient admission will be excluded from the numerator and denominator.

3b. Percent of encounters with an ED revisit measured at 7 days. The numerator will be an ED encounter at any facility included in the INPC database within 7 days of an ED encounter at an intervention or comparator site. ED revisits may serve as the index visit for subsequent revisits. The denominator will be all eligible ED encounters (see **Inclusion criteria**, above). Encounters resulting in an inpatient admission will be excluded from the numerator and denominator.

3c. Percent of encounters with an ED revisit measured at 30 days. The numerator will be an ED encounter at any facility included in the INPC database within 30 days of an ED encounter at an intervention or comparator site. ED revisits may serve as the index visit for subsequent revisits. The denominator will be all eligible ED encounters (see **Inclusion criteria**, above). Encounters resulting in an inpatient admission will be excluded from the numerator and denominator.

1. Percent of ED encounters with primary care visit within 7 days of an ED encounter. The numerator will include all ED encounters with a completed family medicine, internal medicine, OBGYN, or geriatrician visit^64^ within 7 days of the ED visit. The denominator will be all eligible ED encounters (see **Inclusion criteria**, above).

**Other pre-specified outcome measures**

1. Percent of ED encounters where the HRSN CDS intervention was accessed. The numerator will include encounters with access of the social needs section (containing the risk prediction scores) of the Health Dart CDS during the study visit (defined as within 24 hours). Access will be defined as record of the end user visiting the HRSN page in the system user logs. The denominator will be all eligible ED encounters (see **Inclusion criteria**, above). Limited to the intervention site only.
2. Percent of ED encounters where the CDS platform (Health Dart) was accessed. It is possible that our study may increase usage of the overall CDS platform, but not the HRSN intervention portion. The numerator will include encounters with access of CDS platform (Health Dart) during the study visit (defined as within 24 hours). Access will be defined as record of the end user visiting initiating a request to the Health Dart application from the EHR. Any portion of the Health Dart platform (not just the health-related social needs section) is included. The denominator will be all eligible ED encounters (see **Inclusion criteria**, above). Limited to the intervention site only.
3. **Statistical Considerations**

**Power and Sample Size.** This study's sample size is fixed at the number of ED encounters among eligible adult patients at IU Health Methodist and the matched weighted comparison group. Based on historical data, the intervention site served an average of 2,930 adult patients monthly. According to national estimates, we assumed approximately 15% of these visits would be excluded based on disposition to inpatient admission, a transfer, or death23 or were at an Emergency Severity Index level 170. In the past 12 months (01DEC2023 to 30NOV2024), the average 7-day revisit rate for the intervention site was 5.5% and 30-day revisit rate was 10.5%. These were the only outcomes available for preliminary analyses and served as the range of our outcomes. We used PASS version 24’s test for two proportions in a repeated design71 to estimate the power for the above parameters and detect an odds ratio of 0.90 to 0.50. We assumed 18 time points (9 pre and 9 post) and compound symmetry.

With a monthly sample of 2,400 at the intervention site, we would have >80% power to detect an odds ratio of 0.75 if the readmission rate in the comparison group was 5.5%. For a readmission rate of 10.5%, we could detect an odds ratio of 0.80 with >80% power. Even if we excluded half of the intervention site patients, our sample size would still be sufficient to detect an odds ratio of 0.70 with 80% power.

1. **Analytic Plan**

We will describe the study sample using proportions and means. Our primary analysis will be a DiD approach comparing patient-encounter outcomes at the CDS intervention site with a propensity score weighted sample from other EDs. As our primary strategy we adopt an intention to treat analysis approach where all eligible encounters at the intervention ED site will be considered as having been exposed to the treatment regardless of actual use of the CDS. The following weighted regression model will estimate the probability of each outcome:

$${Outcome}_{it}=\alpha_{0}+ \beta_{1}{Treat}_{i}+ \gamma{Post}_{t}+ \delta_{rDD}\left( {Treat}_{i}*{Post}_{t} \right)+Z_{it}+\varepsilon_{it}$$

Patient-encounters are indexed by $i$ and time by $t$. ${Outcome}_{it}$ is a binary indicator representing each study outcome. ${Treat}_{i}$ is a binary indicator of inclusion in the CDS intervention group, i.e., patient- encounters at IU Health Methodist ED. ${Post}_{t}$ is a dummy variable indicating all post-intervention go-live months. $\delta_{rDD}$is the DiD estimator and will test our hypotheses that the CDS intervention is associated with each outcome. $Z_{it}$ is a set of patient-level, time varying adjustment covariates. $\varepsilon_{it}$ is the error term. Standard errors will be robust clustered at the highest level feasible; specifically, we will check for clustering at the clinician and patient levels and adjust accordingly. As described above, all observations will be weighted using the propensity score derived weights. We will compare the weighted model with the unweighted model. Given the length of panel, we will also check for, and correct for, autocorrelation as needed.

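### The stated power belongs to a two-group repeated-measures test on secondary revisit outcomes, not to the planned difference-in-difference test on screening and referral

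*Protocol*

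**What the plan says.** In Statistical Considerations (Power and Sample Size), the protocol uses a PASS "test for two proportions in a repeated design71 to estimate the power for the above parameters", over odds ratios from 0.90 to 0.50. On structure it says: "We assumed 18 time points (9 pre and 9 post) and compound symmetry". The correlation value, alpha, sidedness and comparison-group size are not given.

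The input rates are revisit rates: "the average 7-day revisit rate for the intervention site was 5.5% and 30-day revisit rate was 10.5" percent. The protocol is open about why: "These were the only outcomes available for preliminary analyses and served as the range of our outcomes".

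Three results follow:
- At 2,400 encounters a month, "we would have >80% power to detect an odds ratio of 0.75 if the readmission rate in the comparison group was 5.5" percent.
- The same power is claimed for an odds ratio of 0.80 at 10.5%.
- With half the intervention-site patients excluded, "our sample size would still be sufficient to detect an odds ratio of 0.70 with 80% power". No baseline rate is attached to this third result.

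The Analytic Plan sets a different test: "Our primary analysis will be a DiD approach comparing patient-encounter outcomes at the CDS intervention site with a propensity score weighted sample from other EDs". The Treat × Post coefficient "is the DiD estimator and will test our hypotheses that the CDS intervention is associated with each outcome".

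Under Measures and Outcomes, the primary outcomes are the percentages of encounters screened and referred. Revisits are secondary. Hypotheses 1 and 2 predict increases in screening and referral.

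**The concern.** Two mismatches stand between the power paragraph and the analysis it is meant to support.

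**Estimand.** A two-group test on repeated measurements compares the groups' average levels over all time points. Treat × Post compares changes, so it carries the sampling error of four cells. For the same 18 months of independent encounters its variance is about four times as large. Correlation also acts differently on a level contrast and on a change contrast, so power for one cannot be read across to the other.

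**Outcomes.** The rates and effect directions belong to secondary outcomes. No baseline is given for screening or referral, and no increase is powered. The Intervention section says the sites did not screen universally or systematically. That fixes no rate, but it gives no support for 5.5–10.5% either.

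At stake is how a null result is read. A reader will set it against a claim of more than 80% power that was not calculated for the test or the primary outcomes in question.

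**Working it through.** **Inputs from the protocol.** 2,400 encounters a month (2,930 × 0.85 = 2,490, so 2,400 is slightly cautious); 9 months before and 9 after; rates 5.5% and 10.5%; odds ratios 0.75 and 0.80.

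**Assumed, because not stated.** Comparison group of equal size; two-sided alpha 0.05.

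**Step 1: the protocol's own figures.** For a time-averaged two-group test under compound symmetry, effective n per arm = n × 18 / (1 + 17ρ). OR 0.75 at 5.5% means 5.50% against 4.18%, a difference of 1.32 points. OR 0.80 at 10.5% means 10.50% against 8.58%, a difference of 1.92 points.

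| ρ | OR 0.75, 5.5%, n = 2,400 | OR 0.80, 10.5%, n = 2,400 | OR 0.70, 5.5%, n = 1,200 |
|---|---|---|---|
| 0 | >99.9% | >99.9% | >99.9% |
| 0.3 | 95.5% | 97.3% | 88.3% |
| 0.4 | 89.8% | 93.1% | 79.6% |
| 0.55 | 80.1% | 84.8% | 67.7% |

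The stated results are attainable under the named test. Because ρ is not given, they cannot be reproduced as single values.

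**Step 2: Treat × Post with independent encounters.** Each cell holds 9 × 2,400 = 21,600 encounters. With p the rate in three cells and q the rate in the treated post cell:
- Risk-difference scale: SE = √[(3p(1−p) + q(1−q)) / 21,600]
- Log-odds scale: SE = √[(3/(p(1−p)) + 1/(q(1−q))) / 21,600]
- Power = Φ(|effect|/SE − 1.96)

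Results:
- OR 0.75 at 5.5%: risk difference 0.01317, SE 0.00301, power 99.2%; log odds 0.2877, SE 0.0619, power 99.6%.
- OR 0.80 at 10.5%: risk difference 0.01920, SE 0.00408, power 99.7%; log odds 0.2231, SE 0.0455, power 99.8%.
- The odds ratios with 80% power are about 0.84 and 0.88, not 0.75 and 0.80.

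**Step 3: extra variance.** Multiply the variance by a design effect D. For OR 0.75 at 5.5%:

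| D | Risk difference | Log odds |
|---|---|---|
| 2 | 87% | 91% |
| 3 | 71% | 77% |
| 5 | 50% | 55% |
| 10 | 28% | 31% |

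Power passes below 80% at D ≈ 2.4 (risk difference) or 2.75 (log odds), that is, roughly 2.5 to 2.75.

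**Step 4: primary outcomes.** OR 1.33, independent encounters, 21,600 per cell. The baselines are assumed.

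| Baseline | Log odds | Risk difference |
|---|---|---|
| 0.5% | 33% | 38% |
| 1% | 58% | 64% |
| 2% | 86% | 90% |
| 5% | 99.7% | 99.9% |

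Using the exact mirror of 0.75 (1/0.75 = 1.333), the 64% becomes 65%.

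**The case against.** The strongest reply is that no arithmetic error has been shown. The stated figures are attainable under the named test. With independent encounters the planned test has at least 99% power at both stated odds ratios, so the claim would then be true and cautious. If compound symmetry described the same 2,400 units followed throughout, within-unit correlation would help the change contrast: the variance is 4p(1−p)(1−ρ)/21,600, giving 98.9% power at ρ = 0 and more as ρ rises. The sample size is fixed in any case. All of this stands, and it rules out saying that the trial is underpowered.

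The direction of effect also matters little in itself. Mirrored increases at the same baselines have slightly higher power (above 99.9% for OR 1.33 at 5.5%). The weakness is the unverified baseline, not the sign.

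Three stronger readings are tempting, and the documents do not support them:
- *That the correlation must have been 0.32–0.40, implausible for separate encounters.* Every ρ from 0 to about 0.40 satisfies all three results. If the half-sample result refers to 10.5%, they hold to about 0.55. The lower bound needs the sponsor to have reported the smallest detectable odds ratio on a grid, which is nowhere stated.
- *That the effects are impossible unless the page is opened in at least 24% (or 18%) of encounters.* This assumes opened encounters carry average revisit risk. Opening is voluntary and the tool flags risk levels. At an assumed 11% revisit rate among opened encounters, the floor would be 1.32/11 = 12%.
- *That the power text says nothing about the primary outcomes.* It names the revisit rates as a stand-in for the range of all outcomes and says why.

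What does not stand is that the paragraph serves as it is. Neither reassuring case, independent encounters or a followed cohort, is stated as the basis of the calculation. The model is written for patient-encounters and expects to check clustering by clinician and patient.

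**Conclusion.** The concern holds in limited form. The figures of more than 80% power at OR 0.75 (5.5%) and OR 0.80 (10.5%) are not the power of the planned analysis, and they cover screening and referral only through a disclosed, unverified proxy. They are unsupported for Treat × Post rather than proven wrong.

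For OR 0.75 at 5.5%, power runs from about 99% with independent encounters to about 50–55% at a design effect of 5. For an OR of 1.33 on a primary outcome, it runs from about a third to over 99% as the baseline moves from 0.5% to 5%. These values rest on assumed 1:1 allocation, two-sided alpha 0.05, and assumed design effects and baselines. Hospital-level change at the single treated site could lower power further, but the protocol gives neither a comparator count nor a variance from which to size it.

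**What to change.** Replace the paragraph with power, or the detectable difference, for the Treat × Post coefficient, treating months as repeated cross-sections of encounters.

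1. Give screening and referral first, as increases, from pre-period rates. Until those are extracted, use a baseline grid such as 1%, 5%, 20% and 50%. Then give revisits.
2. State alpha and sidedness, comparison-group size, and the correlation or design effect used.
3. Add a sensitivity range with a hospital-by-period variance estimated from the comparator EDs' pre-period data.
4. Attach a baseline rate to the half-sample result.

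The cost is one recalculation and some less favourable figures. Sample size, design and data collection do not change.

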**Patients:**

- Inclusion criteria:
  - Adults (≥18 years old) who seek ED care at IU Health Methodist or comparator EDs within the Indianapolis, IN MSA.
- Exclusion criteria:
- Present with a critical illness or injury (e.g., severe trauma patients or those with Emergency Severity Index (ESI) classification level 1).
- Have been transferred from another inpatient facility or died during the ED encounter.
- ED visits resulting in hospital admissions.

Recruitment status: Pending (Participants are not yet being recruited or enrolled at any site)

1. **Study Design**

The study will employ a non-randomized pre-post design with a comparison group of propensity-score matched ED patients from the same metropolitan area who were unexposed to the CDS intervention. The analytic strategy will follow a difference-in-difference (DiD) approach. The study protocol does not include blinding, masking, or random assignment. While Health Dart is available to every IU Health ED, the CDS intervention using HRSN risk scores will only be active at the IU Health Methodist ED during the study period. The Health Dart platform is accessible to clinical staff for all patient encounters. The CDS intervention will generate scores for all eligible adult patients. If risk scores cannot be produced (due to system outages or the absence of prior patient data), error messages explaining the reasons will be provided to end users. These encounters will be excluded from the analyses.

1. **Intervention**

The clinician-facing CDS intervention draws extensively on prior work describing clinician, staff, and patient use of HRSN information in the ED, those same stakeholders’ views of prediction modeling of HRSN risk identification and engineering of features relevant to measuring HRSNs, and independent development of the CDS platform. At the time of this study protocol submission, IU Health ED sites screened neither universally nor systematically for HRSNs. However, the ED was staffed with social workers to support patients with identified HRSNs.

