**Subgroup analyses**

We will stratify all analyses using the results of the prediction modeling as this is intended to affect user behavior. Specifically, we will compare outcomes by the “high”, “medium”, and “low” risk categories. Additionally, end user activities may vary by potential HRSN, thus we will stratify by specific HRSNs or the number of different HRSNs identified. Additionally, because our prediction models use historical data, we will stratify results by the number of prior encounters in the previous 12 months to explore the potential role of data availability. Finally, we will examine for possible differences by race, ethnicity, sex, and age.

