**Alternative strategies**

Alternative strategies may be necessary for defining the sample, applying propensity score matching, and conducting analyses. First, the CDS intervention will be voluntary. If daily access of the CDS (i.e usage) is insufficient for modeling, we will shift from our proposed intention-to-treat analysis for all patients to a per-protocol analysis. In a per-protocol analysis, we could focus on encounters among clinicians who were consistent or more frequent users of Health Dart, based on historical system log data. While this approach could introduce selection bias, making it our secondary strategy, it would offer insights into the CDS intervention's associations and outcomes. We would use the non-adopters from the intervention site as the comparison group and generate propensity score weights for this alternative group. Second, we may not achieve balance in our propensity scores. If that occurs, our first choice will be explore the potential effect of our chosen comparator hospitals. We may be forced to draw our sample from a smaller set of hospitals that better match our intervention site’s practice. Alternatively, we could forego weighting and use individual patient covariates in the model or apply a strict matching approach. Additionally, we could consider including other health systems from the state in our comparison group, although this might impact our ability to measure all study outcomes.

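### The primary DiD model limits its covariates to time-varying ones but has no patient fixed effects, so, read literally, sex, race and ethnicity are left out of the outcome model

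*Protocol*

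**What the plan says.** The Protocol's Analytic Plan gives one regression equation for all outcomes. It holds an intercept, Treat, Post, their product, Z and an error term. Four statements matter here.

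- **Unit.** "Patient-encounters are indexed by" i, so the unit is a visit and not a patient followed over time.
- **Group term.** Treat "is a binary indicator of inclusion in the CDS intervention group", which means the intervention ED.
- **Covariates.** Z "is a set of patient-level, time varying adjustment covariates". None is named.
- **Weights.** The intervention ED is compared with "a propensity score weighted sample from other EDs", and "all observations will be weighted using the propensity score derived weights". The same section also plans to set the weighted results beside those of a model without weights.

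Under Alternative strategies, if the scores do not balance, "we could forego weighting and use individual patient covariates in the model" is offered as a fallback. Under Subgroup analyses, "we will examine for possible differences by race, ethnicity, sex, and age", so the study expects to hold these variables.

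**The concern.** Restricting covariates to time-varying ones suits a panel in which each unit has its own fixed effect, because that effect absorbs whatever does not change. This model is a DiD on repeated cross-sections of encounters. Its only group intercept is the site. A fixed patient trait is therefore absorbed by nothing in the equation, and the wording also keeps it out of Z.

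A constant difference in case mix between sites cancels in a DiD, and so does a shift common to both groups, provided the trait's effect is the same in both groups and periods. What does not cancel is a pre-to-post shift at the intervention ED that the comparators do not share. Without randomisation, only the weights and Z stand between such a shift and the estimate. Propensity weights that contrast sites pooled over time do not address it, and in the unweighted comparison model Z is the only adjustment there is.

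**Working it through.** **Scale from the plan's own figures.** Statistical Considerations claims more than 80% power with 2,400 encounters a month, for an odds ratio (OR) of 0.75 at a 5.5% rate and 0.80 at 10.5%.

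- 5.5%, OR 0.75: odds 0.055/0.945 = 0.0582; × 0.75 = 0.0437; risk 0.0437/1.0437 = 4.18%; difference 1.32 points.
- 10.5%, OR 0.80: odds 0.105/0.895 = 0.1173; × 0.80 = 0.0939; risk 0.0939/1.0939 = 8.58%; difference 1.92 points.

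The power claim itself cannot be confirmed, because the within-unit correlation ρ is not given. I took an effective n per arm of 2,400·T/(1 + (T − 1)ρ), with T = 9 or 18, and assumed equal arms and two-sided 5%. Power is then 0.81–0.83 (first case) and 0.86–0.88 (second) at ρ = 0.5, and 0.65–0.66 and 0.70–0.71 at ρ = 0.8. The claim is thus consistent with ρ up to about 0.5. The present point does not depend on it; these effects serve only as a yardstick.

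**Bias formula.** For a binary fixed trait whose effect on the outcome is constant, and which neither Z nor the weights correct:

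bias = (pre-to-post shift in the trait's share at the intervention ED, minus that at the comparators) × (outcome risk with the trait, minus risk without it).

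**Worked example; every input is assumed.** Trait share at the intervention ED is 50% pre and 55% post; at the comparators it is 45% in both periods. Outcome risk is 8% without the trait and 13% with it. The true CDS effect is zero. Each cell's expected outcome is 8% + 5% × share.

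| Weights, trait not in Z | Intervention pre / post | Comparators pre / post | DiD (points) |
|---|---|---|---|
| None | 10.50 / 10.75 | 10.25 / 10.25 | 0.25 |
| Site contrast pooled over periods (comparators moved to 52.5%) | 10.50 / 10.75 | 10.625 / 10.625 | 0.25 |
| Built within each period | 10.50 / 10.75 | 10.50 / 10.75 | 0.00 |
| All four site-by-period cells at 50% | 10.50 / 10.50 | 10.50 / 10.50 | 0.00 |

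Putting the trait in Z also gives 0.00 here, because its effect is constant.

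**Range.** Differential shifts of 2, 5 and 10 points times risk differences of 1, 3 and 5 points give 0.02 (2% × 1%) to 0.50 (10% × 5%) points. The example's 0.25 is 0.25/1.32 = 19% and 0.25/1.92 = 13% of the planned revisit effects.

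**The case against.** **The weights are the main control for case mix.** This is the strongest reply, and much of it stands. A reader might infer that the model adjusts for nothing beyond time-varying covariates. The documents do not support that: every observation is weighted, and nothing says that sex or race is missing from the score. Weights built within period, or over the four cells, would remove the bias in the example. The text at hand does not describe how the weights are made. That detail may sit in an analysis plan not shown, so its absence is no fault. What remains is that the protocol does state the restriction on Z, and that the unweighted comparison model has no weights to fall back on.

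**Triage acuity and age.** A reader might infer that these are shut out too. They are not. The eligibility criteria refer to "Emergency Severity Index (ESI) classification level 1" as a feature of the presentation, so acuity can differ at each visit, and age changes as well. The current wording admits both.

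**Loose wording.** Each encounter occurs once, so the phrase could mean only that covariates are measured at the visit. That reading is possible, and it is a reason to rewrite the phrase: the literal reading remains open to whoever programs the model.

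**Size.** The protocol gives neither a shift nor an outcome difference. With a 45% share and a 5.5% revisit rate, a 5-point difference means 3.25% against 8.25%, which is large for sex or race. The yardstick is also a secondary outcome; no rates are given for screening or referral, so the bias cannot be scaled for the primary outcomes.

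**Subgroups.** A DiD within strata of a trait is not biased by a shift in that trait's share. This helps as a check, but it does not repair the overall estimate.

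**Conclusion.** The concern holds as a defect in how Z is defined. In an encounter-level model without patient fixed effects, limiting covariates to time-varying ones has no rationale and, taken literally, leaves sex, race and ethnicity out of the outcome model.

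It is tempting to go further and say that a change in patient mix will be read as a CDS effect. The documents do not show that. Bias needs three things together: a shift at the intervention ED that differs from the weighted comparators, an association of the trait with the outcome, and weights that do not correct the shift. None of the three is established. The 0.25 points is an illustration within an assumed range of 0.02 to 0.50, not an estimate. The point merits action because the exposure is avoidable at almost no cost, whichever weights are used.

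**What to change.** In the Analytic Plan, drop the time-varying restriction. Define Z as baseline patient and encounter covariates known at or before triage, time-fixed as well as time-varying, including sex, race and ethnicity. Use the same Z in the unweighted comparison model. State that the weights are built so that case mix is balanced across periods as well as sites; weights made within each period and weights over the four site-by-period cells both serve.

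The cost is a change of wording and slight extra analysis work. The protocol already plans subgroup analyses by these traits, so no new data collection is implied. The change is best made before outcomes are examined.

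### With one treated ED and only clinician- and patient-level clustering named, the intervals for Treat×Post omit hospital-by-time variation and are too narrow to the extent that such variation exists

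*Protocol*

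**What the plan says.** The Study Design section states that "the CDS intervention using HRSN risk scores will only be active at the IU Health Methodist ED during the study period". The Analytic Plan describes the primary analysis as "comparing patient-encounter outcomes at the CDS intervention site with a propensity score weighted sample from other EDs". Eligibility places these in "comparator EDs within the Indianapolis, IN MSA", and their number is not given.

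In the model, Treat "is a binary indicator of inclusion in the CDS intervention group", that is, an encounter at the one intervention ED. Post is a single pre/post dummy and the remaining covariates are patient-level. The coefficient of Treat×Post tests every hypothesis.

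On precision, the Analytic Plan begins "Standard errors will be robust clustered at the highest level feasible" and continues in the same sentence "specifically, we will check for clustering at the clinician and patient levels and adjust accordingly". It later adds: "Given the length of panel, we will also check for, and correct for, autocorrelation as needed". No level or method is given for that correction. Hospital is not named as a level of variation anywhere, including in the power calculation, which assumes compound symmetry over 18 monthly time points.

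**The concern.** The Treat dummy removes fixed differences between sites, and the Post dummy removes change shared by all sites. A change in one ED's outcome rate that the others do not share is left over. Staffing, social-work cover, a local screening initiative, crowding or an EHR change could each produce one. Such a change reaches all clinicians and patients at that ED together, so it does not average out over them, and errors clustered at those levels do not see it. Clinician clustering is not a proxy for site clustering either: the Intervention section notes that some clinicians practise both at the intervention site and at other hospitals of the system.

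Site-level change is plausible for the primary outcomes. The protocol says that the system's EDs did not screen universally or systematically at the time of submission, and that social workers support patients with identified needs. A local policy or staffing change could move screening or referral directly.

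At stake is whether an interval for Treat×Post that excludes zero can be read as evidence for the intervention at the nominal error rate.

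**Working it through.** **The plan's own figure.** The protocol states more than 80% power for an odds ratio of 0.75 at 5.5% and for 0.80 at 10.5%, with 2,400 encounters a month. Neither alpha nor the within-unit correlation ρ is stated. I took two-sided 0.05, equal groups and a variance factor of (1+17ρ)/18:
- OR 0.75 at 5.5%: 83% power at ρ = 0.5 and 71% at ρ = 0.7.
- OR 0.80 at 10.5%: 88% at ρ = 0.5 and 76% at ρ = 0.7.

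The statements are therefore consistent with ρ up to about 0.5 but cannot be confirmed. The stated inputs contain no hospital-level component.

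**Size of the effects sought.** An odds ratio of 0.75 at 5.5% gives 0.04125/0.98625 = 4.18%, a difference of 1.3 points. An odds ratio of 0.80 at 10.5% gives 0.084/0.979 = 8.58%, a difference of 1.9 points.

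**Inputs.**
- From the protocol: 2,400 encounters a month and 9 months per period, so n = 21,600 per hospital-period; rates of 5.5% and 10.5%.
- Assumed: number of comparator EDs J, and shock SD τ in percentage points.

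**Formulas.**
- Encounter-level variance of the DiD: V0 = 2c·p(1−p)/n. Here c = 2 if the weighted comparison group counts as 21,600 per period in total, and c = 1+1/J if each comparator ED contributes 21,600.
- Hospital component: Vs = 2τ²(1+1/J)/k, with k = 1 for a shock lasting the whole period and k = 9 for independent monthly shocks.
- Ratio of true to naive SE: R = √((V0+Vs)/V0). Type I error of a nominal 5% test: 2[1−Φ(1.96/R)].

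**5.5% rate, J = 5.** For c = 2, V0 = 4×0.051975/21,600, an SE of 0.31 points. For c = 1.2, the SE is 0.24 points.

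| τ (points) | Pattern | c = 2: R, type I | c = 1.2: R, type I |
|---|---|---|---|
| 0 | none | 1.00, 5% | 1.00, 5% |
| 0.25 | monthly | 1.08, 7% | 1.14, 8% |
| 0.25 | persistent | 1.60, 22% | 1.90, 30% |
| 0.5 | monthly | 1.30, 13% | 1.47, 18% |
| 0.5 | persistent | 2.69, 47% | 3.37, 56% |
| 1.0 | monthly | 1.94, 31% | 2.37, 41% |
| 1.0 | persistent | 5.09, 70% | 6.52, 76% |

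**Check with clinician-clustered errors.** A simulation at the 5.5% rate used 3,000 runs per setting, with 40 clinicians per hospital and 540 encounters per clinician per period (40×540 = 21,600; the split is assumed). Type I error was 5-7% with no hospital shock. It was about 30%, 56% and 75% with persistent shocks of SD 0.25, 0.5 and 1.0. This agrees with the last column and was almost the same for J = 3, 5 and 10. When every ED has the same n, the factor (1+1/J) cancels from R, so adding comparators does not help.

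**10.5% rate, J = 4, each ED contributing 21,600, encounter-level errors.** V0 = 2×1.25×0.093975/21,600, an SE of 0.33 points.
- Monthly shocks of SD 0.5: √(0.109+0.069) = 0.42, R = 1.28, type I error about 12-13%.
- Monthly shocks of SD 1.0: √(0.109+0.278) = 0.62, R = 1.89, type I error about 30%.

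**Hospital-clustered errors.** Ordinary cluster-robust errors at hospital level gave type I error of about 27% (J = 3), 36% (J = 5) and 52% (J = 10). The Treat terms fit the single treated hospital's two period means exactly, so it adds nothing to the estimated variance.

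**The case against.** The strongest reply is that the problem is conditional. The protocol reports no hospital-by-time variation. With none, clinician clustering behaves correctly, and with small independent monthly shocks the loss is minor. That stands. A reader might infer that the intervals are certainly too narrow for every outcome; the document does not support this.

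Second, the general phrase about the highest feasible level might be read as leaving hospital open, or as a principle that the plan then breaks. Neither reading is secure. The rest of the sentence narrows it to clinician and patient. Since hospital clustering fails with one treated ED, clinician may well be the highest level that is feasible for a conventional robust error. The passage is better seen as leaving a design limitation unaddressed than as contradicting itself.

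Third, the plan does undertake to look for autocorrelation. Done on site-month data, this could capture part of the variation. As written it is conditional and without a level, so it cannot be counted on, but false-positive rates that assume no correction for serially correlated shocks should not be attributed to the plan.

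Fourth, the illustrations use revisit rates, which are secondary outcomes. The protocol says these were the only outcomes with preliminary data, so nothing here quantifies screening or referral.

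Finally, a lasting concurrent change at the intervention ED also biases the estimate. That is a failure of parallel trends, and a wider interval does not remove it.

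**Conclusion.** The point holds in conditional form. Treatment is assigned at one hospital, the levels named for clustering lie below the hospital, and no model term reflects hospital-specific change over time. To the extent that such change occurs, the intervals for Treat×Post are too narrow and the false-positive rate exceeds nominal. This is a stated inference rule rather than a detail left open, and the same rule serves all primary and secondary outcomes.

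The size is unknown. It depends on the SD and persistence of the shocks, neither of which the protocol gives, and on how the weighted comparison group is counted. On revisit outcomes the illustrations run from no inflation with no shock, through a modest one (true SE about 8-14% larger) for independent monthly shocks of SD 0.25 points, to roughly 30-75% type I error for persistent shocks of SD 0.25 to 1.0 points. Confidence is high on the text and low on the magnitude. The protocol does not support reading these percentages as the error rates of the trial, or carrying them over to the primary outcomes.

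**What to change.** In the Analytic Plan:

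1. State that treatment is assigned at hospital level with one treated ED.
2. For each primary and secondary outcome, report inference from site-month data that allows for hospital-by-time variation and serial correlation. Options are a DiD method for few treated clusters (Conley-Taber or Ferman-Pinto), or placebo estimates from each comparator ED and from pseudo go-live dates in the pre-period.
3. Label the clinician/patient-clustered intervals as excluding hospital-level variation, and do not base the effectiveness conclusion on them alone.
4. Choose the method before outcomes are examined.

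The work is analysis and programming on data the study will already hold. The limits should be stated with it:
- Intervals will be wider.
- A pure permutation test over J comparators has a smallest p-value of 1/(J+1), so 0.05 needs J = 19. Residual-based methods are also coarse with few EDs, and pseudo-dates within 9 pre-period months overlap.
- The number of comparator EDs is not given. The Alternative strategies section allows for a smaller set, and warns that adding health systems might affect outcome measurement.
- None of this removes bias from a lasting concurrent change at the intervention ED, which has to be addressed as a parallel-trends question.
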